### Analysis of data

The primary efficacy endpoint of the study will be the change in Western Ontario and McMaster Universities Osteoarthritis Index (WOMAC) [31] score from before to after the 6-week, 12-visit trial.

The WOMAC is a widely used, reliable, valid and responsive measure of treatment outcomes in patients with OA of the hip or knee [31]. The WOMAC index consists of 24 questions (5 related to the amount of pain, 2 to stiffness and 17 to physical function), and takes less than 5 minutes to complete [32]. The Likert version of the WOMAC rates each question on an ordinal scale of 0 to 4, with lower scores indicating lower levels of symptoms or physical disability [33].

Secondary efficacy endpoints will include: 1. the success rate of treatment; 2. change in scores on the WOMAC pain subscales; 3. 100 mm pain VAS on walking; 4. results of a 6-minute walk test; and 5.investigator global assessment (IGA)/patient global assessment (PGA). Treatment success will be defined as ≥36% improvement in WOMAC score, and treatment failure by a change <36% in WOMAC score or a missing value [34].The 100 mm pain VAS on walking is used to evaluate the severity of pain. The patient will be asked to walk 15 m in a straight line and to determine his/her level of pain from 0 mm (absence of pain) to 100 mm (worst pain imaginable).The 6-minute walk test, which measures the distance a person can walk in 6 minutes, has been found to reliably measure functional exercise capacity and has been frequently used in OA-related trials [35,36]. For IGA and PGA, the oriental medicine doctor and the patient, respectively, will evaluate general improvements in OA pain-related symptoms, using a five-grade scale: excellent, good, fair, poor and aggravated. The 100 mm VAS on walking, WOMAC pain scale and IGA/PGA will be assessed at baseline, at each treatment session, and 12 weeks after the start of treatment. The WOMAC and 6-minute walk tests will be assessed at baseline, and after 3, 6 and 12 weeks from the start of the trial.

In addition, the patients will be asked to record their symptoms according to a VAS each morning and evening during the duration of the trial. They will also be asked to record the medications they take, such as analgesics and NSAIDs for knee pain, at the beginning of the trial, at each treatment session, at the end of treatment (week 6), and at 12 weeks after the start of the treatment (Table 2).

**Table 2 T2:** Example of outcome measurements

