### Sample size

The primary efficacy parameter is change in WOMAC score from baseline to the end of treatment after 6 weeks. The standard deviation (SD) of the WOMAC score is 3.35 [27]. In calculating the appropriate sample size for this study, we sought to obtain a more conservative SD, with a true mean difference of 2.34.

With *μ*_1_ and *μ*_2_ representing the mean WOMAC scores for the test and control groups, respectively, the null-hypothesis 

$$H_{0}:\mu_{1}-\mu_{2}=0$$

 will be tested versus the alternative hypothesis 

$$H_{1}:\mu_{1}-\mu_{2}\neq 0$$

Using these hypotheses, we calculated the sample size needed to achieve 80% power using the equation: 

n=Zα/2+Zβ2σ2μ1-μ22.

To show that the individualized treatment group is not equal to the control groups, patients will be randomized 2:2:1:1 to the individualized treatment group, standard treatment group, sham group and untreated group, respectively. Using these assumptions and specifications, a sample size of 198 individuals (66:66:33:33) will provide a power of 80% at a significance level of 0.05. To allow for a 20% dropout rate, a slightly higher number, 250 patients, will be randomized in the trial.

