### Statistical analysis plan

All statistical analyses will be performed using SAS version 9.1 or a later version. All statistical tests will be two-sided and the level of significance will be set at 0.05. The last observation carried forward (LOCF) method will be used to input data with dropouts. Continuous variables will be expressed as mean ± SD, and categorical variables as number and percentage.

The primary endpoint will be compared in the four groups by analysis of covariance (ANCOVA),with treatment means adjusted to baseline WOMAC scores as a covariate. Confidence intervals will be derived from ANCOVA. Repeated measures analysis of variance (ANOVA) will also be used to analyze primary and secondary efficacy variables. Categorical data will be analyzed using Pearson’s chi-square test or Fisher’s exact test.

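### Baseline adjustment is stated only for the primary ANCOVA; the continuous secondary endpoints are given repeated measures ANOVA with no baseline covariate stated, although their baselines are collected

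*Protocol article*

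**What the plan says.** Under Statistical analysis plan, the protocol article gives the primary endpoint a baseline-adjusted model: "The primary endpoint will be compared in the four groups by analysis of covariance (ANCOVA),with treatment means adjusted to baseline WOMAC scores as a covariate". It adds "Confidence intervals will be derived from ANCOVA" and then "Repeated measures analysis of variance (ANOVA) will also be used to analyze primary and secondary efficacy variables". Categorical data go to chi-square or Fisher tests. No other method is named for continuous secondary endpoints. On error rates it says "All statistical tests will be two-sided and the level of significance will be set at 0.05".

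Under Sample size, the primary time point is fixed: "The primary efficacy parameter is change in WOMAC score from baseline to the end of treatment after 6 weeks".

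Analysis of data and Table 2 show that every continuous secondary endpoint has a baseline value. The 6-minute walk, like total WOMAC, is measured on 4 occasions (baseline, weeks 3, 6 and 12). WOMAC pain and VAS on walking are measured on 14 (baseline, 12 visits, follow-up); the text reads "WOMAC pain scale and IGA/PGA will be assessed at baseline, at each treatment session" and adds the week-12 follow-up.

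**The concern.** The article uses the baseline value where it describes the primary model and is silent on it for the secondaries, in adjoining sentences. A repeated measures ANOVA run as named can be laid out with baseline as one of the repeated levels, or on post-baseline visits without a covariate. Neither makes full use of the baseline.

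The terms such an analysis yields also do not match the trial's aim, which is to compare individualized acupuncture with standard, sham and no acupuncture. With four groups, the group main effect is an average over visits, including week 12, when treatment has ended. The group-by-time test has 3 x 3 = 9 degrees of freedom with 4 occasions and 3 x 13 = 39 with 14. Neither is a week-6 contrast against one control.

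At stake are precision and interpretability on three secondary endpoints. A smaller matter is that total WOMAC is analysed by two methods, with no sentence saying which decides.

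**Working it through.** **The plan's own figure.** With difference 2.34, SD 3.35, two-sided 0.05 and 80% power, the two-sample 1:1 formula gives 2 x (1.960 + 0.842)² x 3.35² / 2.34² = 32.2, so 33 per group. Doubling the two larger arms gives 66:66:33:33 = 198, as stated. Allowing for 20% dropout, 198 / 0.8 = 247.5, i.e. 248, against 250 stated. No baseline covariate enters, so the sample size does not depend on this point.

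**Inputs for the comparison.** From the article: 66 (individualized) v 33 (sham or untreated), and 4 or 14 occasions. Assumed, because the article does not give them: effect δ = 0.5 SD at every post-baseline visit, compound symmetry, and correlation ρ from 0.3 to 0.7.

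**Formulas.** T is the number of occasions, k = 66 x 33 / 99 = 22, SD = 1. Power is from the noncentral F with noncentrality λ:

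- A. Main effect, baseline as a level: λ = k[δ(T-1)/T]² / V, V = [1 + (T-1)ρ]/T; 1 and 97 df.
- B. Group-by-time, baseline as a level: λ = kδ²[(T-1)/T]/(1-ρ); T-1 and 97(T-1) df.
- C. Post-baseline visits, no covariate: λ = kδ²/V, V = [1 + (T-2)ρ]/(T-1); 1 and 97 df.
- D. Post-baseline visits, baseline as covariate: as C with V reduced by ρ²; 1 and 96 df.
- E. Week-6 ANCOVA alone: λ = kδ²/(1-ρ²); 1 and 96 df.

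**Worked case, T = 4, ρ = 0.5** (kδ² = 5.5):

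- A: effect 0.375, V = 0.625, λ = 4.95, power 59.6%.
- B: λ = 5.5 x 0.75 / 0.5 = 8.25, power 66.3%.
- C: V = 0.667, λ = 8.25, power 81.2%.
- D: V = 0.667 - 0.25 = 0.417, λ = 13.2, power 94.9%.
- E: λ = 5.5 / 0.75 = 7.33, power 76.5%.

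**Power (%) at ρ = 0.3 / 0.5 / 0.7**

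| Analysis | 4 occasions | 14 occasions |
|---|---|---|
| A main effect, baseline a level | 71.5 / 59.6 / 50.7 | 95.4 / 83.8 / 71.9 |
| B group-by-time | 50.4 / 66.3 / 88.6 | 34.8 / 49.5 / 77.1 |
| C post-baseline, unadjusted | 88.9 / 81.2 / 73.8 | 97.4 / 88.6 / 78.0 |
| D post-baseline, baseline-adjusted | 93.7 / 94.9 / 98.6 | 99.5 / 99.1 / 99.8 |
| E week-6 ANCOVA only | 68.2 / 76.5 / 90.2 | 68.2 / 76.5 / 90.2 |

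D exceeds A, B and C at each ρ and for both visit schedules.

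**Dilution.** In A, a constant effect is multiplied by (T-1)/T: 3/4 with 4 occasions and 13/14 (93%) with 14. B, C and D are not diluted in this way.

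**Sensitivity to effect size and time course.** The article's planning values for WOMAC give 2.34 / 3.35 = 0.70 SD. With 4 occasions and ρ = 0.3 / 0.5 / 0.7 (normal approximation for the 1-df tests):

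- Constant effect: D 99.8 / 99.9 / >99.9%; A 94.6 / 87.5 / 79.7%; B 81.7 / 93.2 / 99.6%; C 99.4 / 98.0 / 95.6%.
- Effect at weeks 3 and 12 half that at week 6: D 90.7 / 92.3 / 97.5%; A 66.2 / 54.5 / 46.1%; B 62.7 / 78.7 / 95.5%; C 84.9 / 76.3 / 68.5%; E 93.0 / 96.6 / 99.6%.

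The ordering of D over A, B and C holds, but the gaps narrow when the effect is large. When the effect peaks at week 6, E is the most powerful.

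**Two tests of total WOMAC.** In a simulation under no effect (4 occasions, 20,000 runs per ρ), the chance that at least one test is significant was 9.0-9.3% for ANCOVA or the main effect, and 8.3-8.7% for ANCOVA or group-by-time. Two independent tests would give 1 - 0.95² = 9.75%.

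**The case against.** The strongest reply is that one sentence in an article does not specify a model. It leaves open whether baseline is a level or a covariate, whether score or change is the response, and which term is read, and a fuller plan may settle all three. This stands as a limit. A reader might infer that the repeated measures ANOVA has no baseline covariate; the article shows only that none is stated, in contrast to the ANCOVA.

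Three further inferences go beyond the document.

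- *That the method dilutes the effect.* This needs baseline as a repeated level and the main effect as the term read. Even then WOMAC pain and VAS on walking keep 93% of a constant effect.
- *That it always costs power.* Against a single-visit week-6 ANCOVA it may not. With 14 occasions and ρ = 0.5, the main effect has 83.8% and week-6 ANCOVA 76.5%. With 4 occasions and ρ = 0.3, the figures are 71.5% and 68.2%. The consistent loss is against a baseline-adjusted repeated measures analysis. Sphericity is no general objection either, since the between-group main effect does not need it.
- *That total WOMAC has two unranked tests and an inflated type I error.* ANCOVA is named first for the primary endpoint ("The primary endpoint will be compared in the four groups by analysis of covariance (ANCOVA"), it supplies the confidence intervals, and the repeated measures analysis is introduced as an addition. The natural reading is that ANCOVA decides. The article does not say so, but it does not allow either result to be claimed.

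The 0.5 SD effect is also an assumption, as the article gives no planned effect for the secondaries. At the 0.70 SD planned for WOMAC, with a constant effect, the differences are smaller. None of this removes the gain from adding the baseline.

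**Conclusion.** The point holds as a worthwhile improvement to the secondary analyses. It does not threaten the primary analysis or the sample size. As stated, the plan attaches baseline adjustment to the primary ANCOVA alone and names an analysis for the continuous secondaries whose omnibus terms do not answer the comparison of interest.

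For a constant 0.5 SD effect, 66 v 33, compound symmetry and ρ 0.3 to 0.7, baseline adjustment of the post-baseline visits gives 94-99% power against 50-89% (4 occasions), and 99% or more against 35-97% (14 occasions). Against the best unadjusted version the gain can be small: about 5 points at ρ = 0.3 with 4 occasions and about 2 with 14. The ordering held in every case computed; the size depends on correlation, effect and time course, none of which the article gives for these endpoints.

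The ranking of the two analyses of total WOMAC needs only a clarifying sentence. The 8-9% error rate applies only if either test could be claimed.

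**What to change.** 1. For WOMAC pain, VAS on walking and 6-minute walk, analyse the post-baseline visits with the endpoint's own baseline as covariate, in a mixed model with group, visit and group-by-visit. Choose a covariance structure the data can support. An unstructured matrix over 13 post-baseline visits has 13 x 14 / 2 = 91 parameters, which is debatable with about 200 to 250 patients.
2. Report individualized acupuncture against each control as the week-6 contrast and, where a sustained effect is of interest, as the average over the treatment visits. State in advance which is read first, because their relative power depends on the time course.
3. State that the week-6 ANCOVA is the sole confirmatory analysis of total WOMAC and that the repeated measures analysis of it is supportive.

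The cost is analysis wording and code. No new data are needed, and the article reports that enrollment was still under way.

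### No ordered method is named for the five-grade IGA and PGA; Pearson or Fisher would ignore the grade order, and the ANOVA sentence would need scores the article does not define

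*Protocol article*

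**What the plan says.** The Analysis of data section lists "investigator global assessment (IGA)/patient global assessment (PGA") as the fifth secondary efficacy endpoint. The doctor and the patient respectively rate improvement "using a five-grade scale: excellent, good, fair, poor and aggravated". Ratings are scheduled at baseline, at each treatment session and at the 12-week follow-up.

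The Statistical analysis plan section has two sentences that could govern these ratings:

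- The sentence that opens with "Categorical data will be analyzed using" goes on to offer a choice of two tests, Fisher's and Pearson's, both of which treat the categories as unordered.
- The sentence just before it takes a different route: "Repeated measures analysis of variance (ANOVA) will also be used to analyze primary and secondary efficacy variables".

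Neither sentence names IGA or PGA. The section divides variables into continuous (mean and SD) and categorical (number and percentage), and no ordinal test appears. Testing is fixed by "All statistical tests will be two-sided and the level of significance will be set at 0.05".

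**The concern.** Verbal grades summarised as counts and percentages belong most naturally with the categorical data, and so with Pearson or Fisher. On a table of arms by five grades, those tests ask whether the distributions differ in any way. Shuffling the five grade labels leaves the p-value unchanged. A move from fair to good counts no differently from a move from fair to aggravated. The clinical question is directional: did patients improve more? A test that ignores direction spreads a consistent shift over several degrees of freedom and yields no single effect estimate.

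The other route, repeated measures ANOVA, does use the order, but only after each grade is given a number. The article defines no scores, and the usual 1-to-5 coding treats every step between grades as equal. With both sentences standing and no precedence stated, a reader cannot tell which result is the main one for these endpoints.

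**Working it through.** **1. Arm sizes (from the plan).** No power is stated for IGA or PGA, so the arm sizes come from the WOMAC calculation. "The standard deviation (SD) of the WOMAC score is 3.35", and the stated difference is 2.34. With two-sided 0.05 and 80% power:

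n = 2 × (1.960 + 0.842)² × 3.35² / 2.34² = 2 × 16.09 = 32.17, so 33 per arm.

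With 33 as the smallest arm, 2:2:1:1 gives 66:66:33:33 = 198, as stated. Allowing 20% dropout, 198 / 0.80 = 247.5, so 248, against 250 stated. The plan's figures reproduce. Pairwise comparisons with the individualized arm are therefore 66 v 66 (standard) and 66 v 33 (sham or untreated).

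**2. Order is not used.** Pearson's statistic is the sum over cells of (O − E)²/E, and a sum does not depend on the order of the columns. Degrees of freedom are (2 − 1)(5 − 1) = 4 for a pair of arms and (4 − 1)(5 − 1) = 12 for four arms. A rank test uses 1 and 3.

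**3. Approximate cost of the extra degrees of freedom.** Assume the effect is a pure shift, so that both tests have about the same noncentrality. For 80% power on 1 df that is (1.960 + 0.842)² = 7.85.

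| Power on 1 df | Power on 4 df | Loss (points) |
|---|---|---|
| 50% | 30.8% | 19.2 |
| 70% | 48.2% | 21.8 |
| 80% | 59.5% | 20.5 |
| 90% | 74.0% | 16.0 |
| 95% | 83.7% | 11.3 |

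For four arms, 80% on 3 df becomes 54.9% on 12 df.

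**4. Simulation at the planned sizes.** Assumptions, none from the documents: a comparator grade distribution and a common odds ratio (OR) shifting all grades. Each scenario had 20,000 runs, comparing Pearson with a tie-corrected rank test. For a comparator at 3/12/50/30/5%:

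| OR | 66 v 33: Pearson / rank / loss | 66 v 66: Pearson / rank / loss |
|---|---|---|
| 1.5 | 10.0 / 16.9 / 6.9 | 12.3 / 23.5 / 11.2 |
| 2 | 23.8 / 40.5 / 16.7 | 33.7 / 56.0 / 22.3 |
| 2.5 | 41.0 / 62.0 / 20.9 | 56.8 / 79.2 / 22.4 |
| 3 | 57.0 / 77.8 / 20.8 | 75.7 / 91.8 / 16.1 |
| 3.5 | 70.6 / 87.2 / 16.7 | 86.7 / 96.6 / 9.9 |
| 4 | 80.4 / 93.0 / 12.6 | 93.4 / 98.7 / 5.3 |

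(Powers in per cent; losses in points, taken before rounding.)

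With a comparator at 8/25/37/22/8% and OR 2.5, the results are 43% v 66% (66 v 33) and 60% v 82% (66 v 66). Across the distributions tried, the pairwise loss runs from about 4 to 22 points over OR 1.5 to 4. In the four-arm test at OR 3, with the standard arm given half the log odds ratio, Pearson has 56 to 62% and Kruskal-Wallis 80 to 85%. With no effect, both tests reject about 5% of the time (4.1% and 5.3% in the 3/12/50/30/5% case).

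**The case against.** The strongest reply is that the article never assigns IGA and PGA to chi-square. The ANOVA sentence covers secondary efficacy variables by its wording, these ratings are taken repeatedly, and ANOVA on scores would use the order. The categorical sentence has another clear referent in the binary success rate. This stands in part: a reader might infer that Pearson or Fisher is the fixed test for IGA and PGA, and the text does not establish that. It does not dispose of the point, because the ANOVA sentence cannot sensibly cover every secondary variable (success rate is binary) and the scores it would need are undefined.

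A second reply is that a condensed article leaves endpoint-level tests to the full plan. That would answer silence. Here the article states tests, and neither suits an ordered scale as described.

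Third, a reader might take 20 points as a general loss, or think the planned test invalid or blind to direction. None of these is supported. The loss depends on an assumed proportional-odds shift, which favours ordered tests; no other pattern was tried, and Fisher's test was not simulated. Type I error is held. The planned counts and percentages would show direction descriptively, though the test would not.

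**Conclusion.** The point holds in a limited form. IGA and PGA are ordered, no ordinal method is named, and the two candidate sentences lead respectively to a test that ignores order and to a model on undefined scores. Chi-square is the natural reading but not the only one. If it is used, the consequence is lost efficiency, not error: about 20 points pairwise where a rank test would have roughly 65 to 80% power, and less for weak or very strong effects. Those sizes rest on assumed grade distributions and a common odds ratio; that order is ignored does not. The primary WOMAC ANCOVA is untouched and no power is claimed for IGA or PGA, so this is minor.

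**What to change.** Add one sentence to the Statistical analysis plan: IGA and PGA at week 6 will be compared between arms by an ordered method, and this is the main analysis of these endpoints in place of both chi-square/Fisher and ANOVA. Either of these would serve:

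- a Wilcoxon rank or row-mean-score test, which may be stratified by site since each site has its own randomization list; or
- a proportional-odds model reporting a common odds ratio with its confidence interval.

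Keep chi-square/Fisher for the binary success rate and for unordered categories.

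The cost is one sentence, with no extra data or patients. The only downside is the proportional-odds assumption if the model is chosen; the rank test does not need it for validity. The article reports enrollment as still under way, so at that stage the change could be made before analysis.

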### Randomization and blinding

Patients will be randomized by an independent statistician using a computerized, random-number generator through the block-randomization method of SAS version 9.1(SAS Institute Inc, Cary, NC, USA) for sequence generation. Separate randomization files will be created for each of the two sites. Allocations will be concealed using sealed, opaque envelopes. After the assessor has screened the patient for inclusion and the patient has signed the informed consent form, the next envelope in the sequence will be provided, immediately prior to treatment, to the certified oriental medicine doctor who will perform acupuncture. By this method, a total of 250 participants will be randomly assigned to the four groups. Although all patients and their screening assessors will be blinded to treatment, the certified oriental medicine doctor applying acupuncture will not.

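### The success-rate test ignores the site by which patients are randomised and the baseline WOMAC already collected: a valid choice, but it gives up some efficiency if the two sites differ

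*Protocol article*

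**What the plan says.** The article lists success first among the secondary endpoints: "Secondary efficacy endpoints will include: 1. the success rate of treatment". It defines the endpoint so that every patient is classified: "Treatment success will be defined as ≥36% improvement in WOMAC score, and treatment failure by a change <36% in WOMAC score or a missing value".

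The statistical analysis plan section has one sentence on testing outcomes of this type. It begins "Categorical data will be analyzed using" and names Pearson's chi-square and Fisher's exact test. Such outcomes are to be described as "categorical variables as number and percentage".

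On design, the randomization and blinding section says "Separate randomization files will be created for each of the two sites", so site is a stratification factor. On data, the analysis of data section says "The WOMAC and 6-minute walk tests will be assessed at baseline, and after 3, 6 and 12 weeks from the start of the trial". The primary ANCOVA uses the baseline score, "with treatment means adjusted to baseline WOMAC scores as a covariate". No corresponding adjustment is stated for success, which is derived from the same scale.

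**The concern.** Separate blocked lists keep the arms in nearly the same proportions within each hospital. Differences between hospitals then add almost nothing to the true variability of the treatment comparison. The pooled variance in Pearson's statistic still counts those differences as noise. If the sites have different success rates, the test rejects less often than 5% under the null and has less power than an analysis by site.

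Baseline WOMAC raises a related issue. If it predicts who reaches the 36% threshold, adjusting for it sharpens the comparison at no cost in data. What is at stake is some precision on one secondary endpoint.

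**Working it through.** **The plan's own figure.** The sample size concerns the primary continuous endpoint; no power is given for success. With SD 3.35, difference 2.34, two-sided 5% and 80% power, the usual two-sample form gives 2 × (1.960 + 0.842)² × 3.35² / 2.34² = 32.2, so 33 per smaller arm. Then 33 × (2+2+1+1) = 198, as stated, and 198/0.8 = 247.5, so 248 against the 250 planned. It reproduces and is unaffected by this point.

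**Numbers entering the success analysis.** A missing value is a failure, so I take all randomised patients as entering. 250/6 = 41.7, so about 42 in each of the sham and untreated arms and about 83 in the individualized arm. I used 84 v 42, split evenly over the two sites (42 v 21 at each).

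**Assumptions, not in the documents.** A common odds ratio of 3.2; comparator success averaging 30% over the sites; equal site sizes. At 20%/40%, for example, the comparator odds are 0.25 and 0.667. Multiplied by 3.2 they become 0.80 and 2.13, so success on individualized treatment is 44% and 68%.

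**Tests compared**, both against 3.841 without continuity correction:
- Pearson on the pooled 2×2 table.
- Cochran-Mantel-Haenszel (CMH): [Σ(A − rc/N)]² / Σ[r(N−r)c(N−c) / (N²(N−1))], summed over sites. A is successes on treatment, r the treated, c all successes and N the patients at the site.

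Power and type I error come from summing the exact binomial probabilities over all possible tables.

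| Comparator success by site | Between-site odds ratio | Power, Pearson | Power, CMH | Type I error, Pearson | Type I error, CMH |
|---|---|---|---|---|---|
| 30% / 30% | 1.0 | 85.4% | 85.4% | 5.1% | 5.0% |
| 20% / 40% | 2.7 | 81.7% | 82.7% | 4.6% | 5.0% |
| 15% / 45% | 4.6 | 75.6% | 79.7% | 3.9% | 4.9% |
| 10% / 50% | 9.0 | 64.0% | 74.2% | 3.0% | 4.9% |

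**Hand check of the conservatism at 20%/40%.** Pooled variance is 0.30 × 0.70 = 0.21. The mean within-site variance is (0.16 + 0.24)/2 = 0.20. The ratio is 0.952 and its square root 0.976. The effective cut-off is 1.96/0.976 = 2.01, a two-sided error of about 4.5%, in line with the table.

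**Sensitivity to numbers.** With 66 v 32 patients, power is 75.5% v 75.5%, 70.8% v 72.0% and 63.7% v 68.4% for the first three rows. For individualized v standard (84 v 84) it is 96.0% v 96.0%, 94.3% v 94.6% and 91.1% v 93.0%.

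**Baseline WOMAC.** Assume a baseline mean of 50 (SD 15) and a week-6 mean of 38 or 32 (SD 17). Adjusting for baseline cuts the standard error of the risk difference by 0.2–2.3% when the baseline–week-6 correlation is 0.3 to 0.7, and by 6.5–7.5% at 0.85. A separate simulation used 83 v 42, success 30% v 55% and 1,500 runs per scenario. Logistic regression on site and baseline raised power over chi-square by about 8–9 points when baseline was strongly prognostic (log odds ratio 1 per SD). With no site or baseline effect it still showed 78.4% v 77.1%. Its null rejection rate ran from 4.6% to 6.1%, so a point or so of the gain may reflect a slightly liberal likelihood-ratio test.

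**The case against.** The strongest reply is that nothing here is wrong. An unadjusted test of a binary secondary endpoint is valid, and preferring a stratified one is a matter of efficiency. That stands, and it sets the weight of the point. The point remains because the article names the test rather than leaving it open, and a better use of the design costs nothing.

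Second, the documents give no reason to expect the sites to differ much. Both use the same eligibility criteria, training workshop and written protocols. This also stands. It does not exclude a site effect, but it makes the lower rows of the table hard to rely on.

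Third, success is already a percentage change from baseline, so baseline WOMAC may add little. This is fair: at moderate correlations the saving is small.

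Two stronger readings are tempting. A reader might infer that the chi-square will be run once across four groups, with three degrees of freedom, and so answer none of the individualized-versus-control questions. The text does not say so. The four-group wording belongs to the ANCOVA sentence, and the sample size section frames the hypothesis as test against control. A reader might also infer from "Confidence intervals will be derived from ANCOVA" that success will have no interval or effect estimate. An article commonly leaves that to the full plan, so its absence here is not a fault.

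**Conclusion.** The point holds as a minor loss of efficiency. The stated tests ignore a factor used in randomisation and a covariate already collected. Under the assumptions above, stratifying by site changes nothing if the sites are alike, adds about one point of power at 20%/40% and about four at 15%/45%. That last case already needs a between-site odds ratio of 4.6.

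A reader might take the bottom row of the table as showing a seriously miscalibrated test. It needs a between-site odds ratio of 9, which nothing in the documents supports. Even there the error is on the conservative side, so false positives are not inflated and the comparison is not biased. The gain from baseline WOMAC cannot be sized from the documents. The primary endpoint and the sample size are untouched.

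**What to change.** Replace the generic sentence, for the success endpoint, with a specified analysis of week-6 success (matching the primary time point) for individualized v each control. Either of these would do:
- a Cochran-Mantel-Haenszel test stratified by site, with the stratified risk difference and its 95% confidence interval; or
- a logistic model with site and baseline WOMAC, reported as a standardised risk difference with its 95% confidence interval.

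The first is the simpler choice and recovers the loss from site. The second also uses baseline WOMAC, and its small-sample error rate should be checked before it is adopted. Chi-square or Fisher's exact can stay for descriptive categorical comparisons. The cost is one sentence in the plan, with no new data and no change to sample size. The article reports enrolment as still under way, so the change can be made before results are known.
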